## Abstract

In spite of the large number of nutrient-derived agents demonstrating promise as potential chemopreventive agents, most have failed to prove effectiveness in clinical trials. Critical requirements for moving nutrient-derived agents to recommendation for clinical use include adopting a systematic, molecular-mechanism based approach and utilizing the same ethical and rigorous methods such as are used to evaluate other pharmacological agents. Preliminary data on a mechanistic rationale for chemoprevention activity as observed from epidemiological, *in vitro* and preclinical studies, phase I data of safety in suitable cohorts, duration of intervention based on time to progression of preneoplastic disease to cancer and the use of a valid panel of biomarkers representing the hypothesized carcinogenesis pathway for measuring efficacy must inform the design of phase II clinical trials. The goal of this paper is to provide a model for evaluating a well characterized agent- Polyphenon E- in a phase II clinical trial of prostate cancer chemoprevention.

## The Disease: Prostate Cancer

The American Cancer Society estimates that there will be 240,890 new cases of prostate cancer (CaP) in the United States (US) in 2011, and 33,720 men will die from this disease [1]. The initiation and progression of CaP involves a complex array of both exogenous and endogenous factors [2-5]. In prostate epithelial tissues, genetic progression and loss of cellular control functions are observed as the cell and tissue phenotype changes from normal to dysplasia (prostatic intraepithelial neoplasia or PIN), then to increasingly severe dysplasia (high grade PIN or HGPIN), to superficial cancers and finally to invasive disease [3]. Although it is clear that clinical CaP incidence and mortality vary greatly between populations, the frequency of latent CaP is evenly distributed among populations, suggesting that external factors such as diet, physical activity and other lifestyle factors are important in the transformation from latent into more aggressive, clinical cancer [2-5]. The features of prostate cancer, namely high prevalence, long latency, significant mortality and morbidity, and the availability of HGPIN and ASAP as intermediate predictive stages of progression, provide the most promise for evaluating agents for chemoprevention [6-9].

Studies indicate that HGPIN is the primary premalignant lesion of CaP [3,10-13] and it is therefore considered a possible pre-invasive precursor of CaP [3]. More recently, atypical small acinar proliferation (ASAP), characterized by a focus of glands that do not contain sufficient cytologic or architectural atypia to establish a definitive diagnosis of cancer [4,14], has emerged as a diagnosis of exclusion but with a greater association to prostatic carcinoma than HGPIN. Both HGPIN and ASAP are associated with progressive abnormalities of phenotype and genotype, which are intermediate between normal prostatic epithelium and cancer, indicating impairment of cell differentiation and regulatory control with advancing stages of prostatic carcinogenesis.

## Prostate Cancer Chemoprevention

Chemoprevention refers to the inhibition of preinvasive and invasive cancer and its progression or treatments of identifiable precancers [8,15]. Chemoprevention efforts require a thorough understanding of the mechanism of carcinogenesis including signaling and metabolic pathways and genetic progression pathways. New technologies in genomics and proteomics have spurred this field of research. The use of this knowledge to develop pharmacologic agents (including nutrient-derived) to reverse or halt the process of carcinogenesis is called chemoprevention. Agents for chemoprevention include anti-promotion and anti-progression agents that prevent the growth and survival of cells that are already committed to become malignant [8,15]. Several nutrient-derived agents have demonstrated promise as potential chemopreventive agents in the prevention of prostate cancer. The goal of this paper is to provide a model for utilizing a systematic approach in planning and evaluating a well characterized agent- Polyphenon E in a phase II clinical trial for prostate cancer chemoprevention.

## Promising Agent for Chemoprevention of Prostate Cancer: Green Tea Polyphenols (GTP)

The use of green tea for prostate cancer chemoprevention has been the focus of many laboratory and clinical studies. The chemopreventive actions of green tea are attributed to the presence of green tea catechins (GTCs), especially epigallocatechin gallate (EGCG) [16]. Clinical studies suggest that GTCs are effective in the chemoprevention of human prostate cancer [17-19]. This prior data justifies the rationale for men with HGPIN and ASAP as a target high-risk population for evaluating promising chemopreventive agents for the prevention of prostate cancer, as we have in this ongoing phase II clinical trial of Polyphenon E.

## Agent Selection and Description

EGCG is the major and most active catechin in green tea and is the most commonly studied GTC *in vitro*, because of its relative abundance in green tea extracts and strong cancer preventative properties [20-22]. However, EGCG has low rates of absorption and bioavailability when administered orally [23-25] and studies indicate that whole mixtures of GTCs may more accurately reflect the human consumption of green tea. This is possibly due to the fact that tea constituents other than catechins may also have anti-carcinogenetic activity and the combined interaction of tea components and catechins may contribute to the effectiveness of the anticarcinogenic activities of GTC mixtures [25-29]. The lack of assurance of infusion contents, differences in tea origin and brewing techniques, all which affect the tea catechin content, have made it necessary to use more standardized GTC mixtures for clinical purposes [30].

Based on the safety profile established in phase I clinical trials [24,31,32], we selected a standardized decaffeinated botanical formulation of green tea catechins, Polyphenon E (Mitsui Norin Co., Ltd., Shizuoka, Japan; Mitsui Norin) for use in this clinical trial. Polyphenon E, is a botanical drug substance containing a mixture of catechins originating from the leaves of green tea (Camellia sinensis). The final product contains 85-95% total catechins; the main component is EGCG, which comprises 56-72% of the material. Other catechins present in Polyphenon E include EC, ECG, EGC, GCG, GC, CG and catechin. Polyphenon E contains minimal amounts of caffeine (<1.0%) and may also contain small quantities of theobromine (<1.0%) and gallic acid (<0.5%). The investigational product used in this study is a hard gelatin capsule containing enough Polyphenon E to deliver 200 mg EGCG per capsule. Placebo capsules are hard gelatin capsules containing pregelatinized starch, microcrystalline cellulose, colloidal silicon dioxide, and magnesium stearate. Both are manufactured under contract to NCI, DCP in compliance with current good manufacturing practice regulations and packaged in 150 cc white HDPE bottles, with 100 capsules per bottle. An investigator-initiated IND was obtained for this agent at this dose and for this indication.

## Hypothesis and Objectives

Our broad and long-term goal is to develop safe, non-toxic agents that can be consumed safely over long periods to prevent progression in men at high risk of prostate cancer using validated markers relevant to prostate carcinogenesis and to monitor changes in disease incidence. Based on the strong preliminary evidence from epidemiological, preclinical, laboratory and early phase I and II pilot studies, the central hypothesis for this Phase II clinical trial is that men with HGPIN or ASAP who receive Polyphenon E at a dose of 400 mg EGCG per day for 12 months will have significantly decreased progression of HGPIN or ASAP to prostate cancer compared with men with HGPIN or ASAP who take placebo.

GTCs have been shown to exert anticancer activities through a variety of different mechanisms [9,30,33-35]. We have proposed a novel cumulative model in which six major mechanisms of GTP chemoprevention (Figure 1): proteasome inhibition, cell cycle arrest, inhibition of cell proliferation, apoptosis, suppression of progression and inhibition of metastasis, work sequentially and in concert through the NFκB pathway to exert chemopreventive action on prostate cancer cells [36]. We hypothesize that the primary pathway by which GTCs in Polyphenon E, specifically EGCG, will induce prostate epithelial cell apoptosis, is via the proteasome inhibition pathway (accumulating IκBα and p27 proteins, decreasing NFκB activation), resulting in inhibition of prostate cell survival and induction of apoptosis, thereby decreasing progression from HGPIN or ASAP to prostate cancer.

## Secondary Study Objectives

The primary objectives of this study are to evaluate the effectiveness and safety of Polyphenon E (200 mg EGCG BID) (vs. placebo) administered for 1 year to men, following the diagnosis of HGPIN and/or ASAP. The primary efficacy endpoint is the progression to prostate cancer at one year. Men will be examined at three (ASAP) and six months (both) for a rise in PSA, as defined by a re-confirmed PSA increase of >0.75ng/ml or the development of a prostate nodule, and biopsied at 3 or 6 months if a rise in PSA or a nodule is detected, or after 12 months and the frequency of HGPIN, ASAP and CaP defined. If prostate cancer develops during the course of investigation, we will compare the extent and grade of the cancer following treatment. The primary safety endpoint is the incidence and severity of AE's during intervention evaluated using standard assessment of toxicity (ver. CTCAE 3.0) [37] based upon detailed questionnaires, including symptoms, clinical evaluation, and assessment of biological samples (comprehensive metabolic panel (CMP), complete blood count (CBC) and LFTs (SGOT/SGPT) completed by Quest Diagnostic laboratories throughout the study. Compliance to intervention is monitored using pill counts and agent logs, quarterly diet diaries and plasma catechins using HPLC-EC at baseline, 6 and 12 months. The effect of treatment with Polyphenon E on lower urinary tract symptoms using the Lower Urinary Tract symptoms Scale [38] and quality of life (QOL) using Rand Short-form (SF)-36 [39] is also evaluated.

Secondary objectives include an exploration of the fundamental molecular pathways that contribute to the chemopreventive activity of Polyphenon E in the prostate. The goal is to determine whether Polyphenon E (200 mg EGCG BID) (vs. placebo) administered for one year results in inhibition of proteasome activity, suppression of cell proliferation and induction of apoptosis in prostate tissue biopsies. In addition, we will explore other plausible pathways by which Polyphenon E may reduce carcinogenesis including stabilization and accumulation of the tumor suppressor p53 and the pro-apoptotic protein Bax, and the inhibition of VEGF (with inhibition of angiogenesis), and MMP-2 and MMP-9 (markers of angiogenesis which mediate invasion and metastasis) [40]. In addition to developing and refining the fundamental pathways of Polyphenon E, these exploratory studies have the potential to define surrogate endpoints for cancer incidence in the prostate.

## Study Design

This 5-year project is a randomized double-blind placebo controlled phase II clinical trial examining the safety and efficacy of Polyphenon E at a dose of 200 mg EGCG bid administered for 12 months versus placebo on the occurrence of cancer in men with a diagnosis of HGPIN or ASAP. Cohort participants are recruited from nine research sites in the United States. We have established special teams for administration, recruitment, intervention and retention, biomarkers and data safety monitoring who work closely to provide efficient, standardized and centralized services for successful implementation of this proposal. In addition to disease progression as the ultimate outcome in this study, we will also evaluate a selected combination of biochemical (PSA, steroid hormones), morphological (cytopathology, Ki-67) and apoptotic index- intermediate endpoint biomarkers relevant to prostate carcinogenesis. We have also included markers of quality of life and exploratory studies examining the molecular targets of Polyphenon E.

## Screening, Registration and Run-in Procedures

The subjects for this study are recruited primarily from Urology and Urology Oncology clinical practices as approved by Institutional Review Boards at each site. The study population consists of men who meet the following eligibility criteria: (a) ages 30-80; (b) diagnosis of HGPIN and/or ASAP within 6 months; (c) PSA≤ 10 ng/ml; (d) No history of cancer except for non-melanoma skin cancer; (e) No known history of hepatic or renal disease (LFTs (SGOT/SGPT) < 2.5 × upper limit of normal, Actual creatinine clearance of >60 utilizing the Cockroft-Gault formula (1976); (f) men who do not or can refrain from drinking six servings of hot tea or 12 servings of iced tea per week or taking green tea supplements; (g) not taking steroid hormones or medications which have known impact on PSA, and; (h) ECOG performance status of 0-1. Eligible subjects are invited to participate and begin screening and run-in procedures. Informed consent is obtained prior to any data collection. Data collected at screening/pre-randomization include lab values for prostate specific antigen (PSA), comprehensive metabolic panel (CMP), complete blood count (CBC), direct bilirubin, prothrombin time/partial thromboplastin time (PT/PTT) and lactate dehydrogenase (LDH). Medical history and concomitant medications are verified and subjects complete a demographic questionnaire. For the run-in period, subjects are instructed on completion of the study agent intake log and the 2-day diet recall with forms provided. A 10 day supply of multivitamin/mineral supplement is provided and subjects are instructed to take once daily until they return to the clinic. The screening and run-in period takes place over a 7-10 day period and is designed to assure ability to maintain compliance with agent intake and required study logs.

## Randomization

Final eligibility is confirmed based on the screening tests and compliance during the run-in period (multivitamin/mineral intake and completion of required study logs). Baseline lower urinary tract symptoms (LUTS) and quality of life (QOL) questionnaires are completed; 2-day diet recall forms are collected and reviewed; signs/symptom assessment is completed and concomitant medications are reviewed. Serum and plasma samples are collected for baseline diagnostic marker analysis, baseline catechin measurements and banking. Urine is collected for baseline diagnostic marker analysis and tissue from diagnostic biopsy is collected for baseline measurements and banking.

Randomization (Polyphenon E, 200 mg EGCG bid or placebo) occurs once a subject is confirmed to meet all eligibility requirements using the SRAR system. SRAR is a web delivered application that records subject registrations and provides blocked randomization assignments using randomization lists developed by our biostatistics department to stratify by diagnosis (HGPIN or ASAP) and by recruitment site, and to ensure that a corresponding placebo and treatment assignment is planned for each strata. Users are securely logged in and then enter subject's registration information. A number corresponding with one of two arms is assigned and an email is sent to the site trial coordinator (blinded) and pharmacy designee (unblinded) stating the treatment/randomization assigned to the subject. As this is a double-blinded study the assignment is hidden from both the subject and investigators.

## Adherence/Compliance during Intervention and Treatment

During study participation, instructions are provided to self administer one capsule of study agent daily each morning and evening, with meals. On the day of the biopsy, subjects are instructed to take the pill with lunch if they have an afternoon appointment. In addition to taking the study agent, subjects are instructed to continue to take one multivitamin/mineral daily. Subjects are also asked to: complete diet recall forms at specified time periods, limit consumption of tea and foods containing high levels of catechins, avoid herbs and nutritional supplements containing catechins, complete daily study agent intake logs, record concomitant medications, and any signs or symptoms. The goal is to maintain ≥85% compliance with study agent intake. Subjects return for monthly visits for the next twelve months.

## Pathological Review

To assure inter-tester reliability of diagnosis of HGPIN (exclusive) or ASAP at all sites, in addition to using one standard diagnosis criteria, at various time points slides from each coordinating site are forwarded for review by the sponsoring site pathologist and the diagnosis verified for consistency. At points of discrepancy between the two pathologists, a third neutral senior pathologist reviews the slide and provides his finding. In addition, quality control studies to confirm diagnosis of HGPIN are done on samples from each site using the PIN-4 stain protocol.

## Monitoring

All subjects are assessed clinically for toxicities during screening (prior to randomization), monthly during intervention, and at the end of intervention. All monthly visits include lab work for safety monitoring (hepatic function panel, PT/PTT and LDH). In addition to regular monthly labs, CBC, CMP, direct bilirubin and PSA are completed at months 3 (PSA only for men with ASAP), 6 and 12 or end of treatment. Compliance with study agent intake is measured during monthly safety checks via pill counts. Study agent intake logs are used to assess signs/symptoms and concomitant medications. Any toxicities (adverse events) occurring during the investigation are reviewed by the treating physician and managed according to standard medical practice.

Clinical procedures are as follows: DRE (month 3 -ASAP; month 6 and 12-all); repeat biopsy (month 3-if palpable prostate nodule or confirmed rise in PSA-ASAP; month 6-ASAP or palpable prostate nodule or confirmed rise in PSA-HGPIN; month 12-all); physical exam (month 12). Additionally, the following data or samples are collected at varying time points: 2-day diet recall, LUTS and QOL (months 3, 6, 12); Serum and urine for diagnostic marker analyses; plasma for catechin measurements; serum for banking (months 6 and 12). Seven+- 3 days post-treatment with study agent, telephone contact is made to assess signs/symptoms and concomitant medications during this time. Study participation is considered complete following this contact.

## Treatment Interruption or Termination

Rules for dose suspension and discontinuation are determined by the type (related to liver function or other) and grade (as determined by CTCAE Term v 3.0) of adverse event. Per FDA requirement, following any recurrent grade 1 LFT elevation (second occurrence of the same elevation) study drug is withheld for at least one week and liver function is monitored until resolution to normal. Following any LFT elevation grade ≥2, study drug is permanently discontinued and liver function monitored until resolution to normal. Study drug is also permanently discontinued for grade 3 and 4 AEs, unless clearly not related to therapy. There are no reductions in the Polyphenon E dose; if AEs occur that require suspension of drug administration, the dose remains the same once treatment resumes. If a subject has an unresolved AE at the time of withdrawal from study treatment, he will be followed until resolution of the event, if possible. If an AE persists for more than 30 days after a subject goes of agent, the subject will be referred to his personal physician.

## Statistical Analysis

The original assumptions for the statistical power calculations for this study were derived from a preliminary study by [name] et al. [18]. Based on recent studies, with ASAP gaining ground as a separate diagnosis, one-year progression rates for exclusive HGPIN range from 4.5% to 27%, centering around 20%. Meanwhile one-year progression rate estimates to prostate cancer for men with ASAP range from 25% to 59%, centering around 40%. Since we anticipate a 50-50 mixture of these two diagnoses, the estimated overall one-year progression rate for this study is 30%. To be conservative, the sample size is chosen to achieve 80% power if the treatment reduces the rate of prostate cancer within one year from 30% to 15%, a 15% reduction compared to the 27% decrease (from 30% to 3%) observed by [name] et al. [18]. The use of blocked randomization with diagnosis being one of two strata will ensure a balance of diagnoses in the two study arms. The analysis will be done overall using a single 2×2 unconditional test.

We plan to perform an interim analysis of the primary endpoint. The α level for the interim look will be .0125, leaving α = .041 for the final analysis. For an unconditional test at the two-sided 0.041 significance level, this requires 123 per group, for a total of 246. The interim look will be made when the first third of the patients (40 per group) has been on study for one year, which is when the primary endpoint is resolved for these patients. This is expected to occur at about the half-way time point in the study. The power for early termination will be 19% if the true cancer rates are 30% and 15%. If the true cancer rates are the same as the sample estimates from the Bettuzzi study, though, the power of early termination will be 85%. Thus, this interim analysis helps to guard against large but conceivable differences in cancer rates between the treatment arms.

In order to achieve 240 evaluable subjects, we will accrue a total of 272 subjects, which allows for an estimated dropout rate of 10% during the run-in phase prior to randomization. This will provide us with 80% power for rates of 30% vs. 15% and 98% power if those rates are 30% and 10%. We also have 87% power for rates of 25% vs. 10%, and 85% power for rates of 20% vs. 7% and 85% power for rates of 15% vs. 4%. With the current sample size, the study will have greater power to detect a 15% difference even where the control group rates will be lower than 30%. In order to assess the effect of treatment on the extent of prostate cancer in those subjects who do develop prostate cancer while on study, we will use the following Gleason grade categories: 0 (for all subjects not diagnosed with prostate cancer), 1–6, 7–8, 9–10, and apply a Tukey trend test at α = .05 to the 2×4 contingency table.

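### Randomisation is stratified by diagnosis but the primary test pools the diagnoses: a mildly conservative choice that costs about 1 to 2 points of power at the planned rates

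*Protocol article*

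**What the plan says.** The Randomization section describes blocked lists built "to stratify by diagnosis (HGPIN or ASAP) and by recruitment site". The Statistical Analysis section gives the purpose: "The use of blocked randomization with diagnosis being one of two strata will ensure a balance of diagnoses in the two study arms".

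The same section treats diagnosis as a strong predictor of the endpoint. For HGPIN it says "one-year progression rates for exclusive HGPIN range from 4.5% to 27%, centering around 20" per cent; for ASAP, "men with ASAP range from 25% to 59%, centering around 40" per cent. It combines the two: "Since we anticipate a 50-50 mixture of these two diagnoses, the estimated overall one-year progression rate for this study is 30" per cent. The sample size is set to "achieve 80% power if the treatment reduces the rate of prostate cancer within one year from 30% to 15" per cent, with 123 per group at two-sided 0.041 after an interim look at 0.0125. A later paragraph of that section plans for 240 evaluable men, or 120 per arm.

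The primary test is then fixed: "The analysis will be done overall using a single 2×2 unconditional test". Neither diagnosis nor site enters it. This is a stated choice, not a detail left to an unseen analysis plan.

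**The concern.** When a prognostic factor is balanced by design, chance differences between arms in that factor no longer add to the variance of the treatment contrast. A pooled 2×2 test still uses a variance that includes them. Its null distribution is therefore narrower than it assumes: it rejects less often than its nominal level and gives up some power compared with a test stratified by the same factor. Both effects grow with the gap between the two diagnoses, and the quoted ranges leave that gap wide open.

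What is at stake is efficiency in a phase II trial with little spare power, not protection against a false claim of benefit.

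**Working it through.** **Inputs** (Statistical Analysis section): control rates 20% and 40%; 50:50 mix; overall 30% against 15%; two-sided alpha 0.041 (critical value 2.0435); 123 per group, or 120 per group evaluable. Assumed: an exact 50:50 split of diagnoses in each arm, no site effect, and the treatment-effect patterns named below, because the article gives no stratum-specific effects.

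**1. The plan's own figure.** The unpooled formula gives n = (2.0435 + 0.8416)² × (0.30×0.70 + 0.15×0.85) / 0.15² = 8.324 × 0.3375 / 0.0225 ≈ 125 per group, against the stated 123. Full enumeration of an exact unconditional test based on the pooled Z statistic gives 78.5% power at 123 per group, against the stated 80%. The stated figure is reproduced within 2 men per group, or within 2 points of power.

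**2. Size at 20%/40%.** Pooled variance: 0.30×0.70 = 0.21. Average within-diagnosis variance: (0.20×0.80 + 0.40×0.60)/2 = (0.16 + 0.24)/2 = 0.20. The effective critical value is 2.0435 × √(0.21/0.20) = 2.094, so the true two-sided size is about 0.036. Simulation of the asymptotic pooled Z gives 0.037. Enumeration of the exact unconditional test gives 0.034 (0.039 if both diagnoses had 30%). CMH by diagnosis gives about 0.041.

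**3. Power at 20%/40%, closed form, 120 per arm, rates halved to 10%/20%.**
- True SD of the difference: √[(0.20 + 0.125)/120] = 0.05204.
- Pooled SE: √[2 × 0.225 × 0.775/120] = 0.05391. Power = Φ[(0.15 − 2.0435×0.05391)/0.05204] = Φ(0.765) ≈ 77.8%.
- Stratified SE: √[2 × ((0.15×0.85 + 0.30×0.70)/2)/120] = √[2 × 0.16875/120] = 0.05303. Power = Φ[(0.15 − 2.0435×0.05303)/0.05204] = Φ(0.800) ≈ 78.8%.

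**4. Planned test (exact, enumerated) against asymptotic CMH (simulated), control rates 20%/40%.**

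| Effect | Per arm | Pooled | CMH | Gap |
|---|---|---|---|---|
| Rates halved | 123 | 79.0% | 80.4% | 1.4 |
| Common odds ratio 0.40 | 123 | 79.0% | 80.5% | 1.5 |
| 15 points off each | 123 | 79.1% | 81.3% | 2.2 |
| Rates halved | 120 | 77.6% | 79.3% | 1.7 |
| 15 points off each | 120 | 77.9% | 80.5% | 2.6 |

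For 80% power with halved rates, the pooled test needs about 126 per arm and CMH about 122 to 123, a difference of 3 to 4 men. Part of this gap comes from replacing an exact critical value by an asymptotic one. At 123 per arm with halved rates, the asymptotic pooled Z has 79.8%, so stratifying alone adds about 0.6 points (80.4 − 79.8).

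**5. Other rates within the quoted ranges.** 120 per arm, rates halved, both tests asymptotic:

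| HGPIN/ASAP | Pooled size | CMH size | Pooled power | CMH power |
|---|---|---|---|---|
| 20%/40% | 0.037 | about 0.041 | 78.6% | 79.3% |
| 10%/50% | 0.023 | 0.041 | 79.9% | 83.6% |
| 4.5%/59% | 0.012 | 0.041 | 84.6% | 90.5% |

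Where the rates are close the choice does not matter: 27%/25% gives 69.9% pooled against 69.8% CMH, 27%/40% gives 84.2% against 84.2%, and 20%/25% gives 61.7% against 61.8%. With 30% in both diagnoses it is 78.1% against 77.9%.

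**6. Interim look** (40 per group, alpha 0.0125, rates halved). At 20%/40% power is 18.1% pooled against 18.4% CMH; at 10%/50%, 16.7% against 21.0%; at 4.5%/59%, 17.0% against 27.5%.

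**7. Exact conditional stratified test.** At 120 per arm and 20%/40% with rates halved, power is about 74.5% to 75%, with size 0.029. The planned exact pooled test has about 77.6%.

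**The case against.** An overall unconditional comparison is valid, openly stated, and the test for which the sample size was calculated. The article gives balance as the reason for stratifying and never counts on a gain in precision. A reader might infer that pooling leaves the trial short of its promised power; the documents do not support that. Under 20%/40% with halved rates the pooled test has 79.0% at 123 per group, slightly above the 78.5% it has when everyone shares the planned 30% and 15%. The loss exists only relative to a stratified test.

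A reader might also infer that ignoring a stratification factor makes the test invalid. Here the error is on the safe side. The different biopsy schedules for ASAP and HGPIN apply equally in both arms and do not change this.

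The larger losses need rates well away from the planning values: 10%/50% is an illustrative pair, and 4.5%/59% joins the lowest HGPIN figure to the highest ASAP figure. The ranges overlap, and near the overlap nothing is gained. All of this stands and limits the weight of the point.

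What remains is that the article itself plans for a twofold difference in rates, already randomises by diagnosis, and can use that at almost no cost.

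**Conclusion.** The point holds as a minor efficiency improvement. At the planned rates the pooled test has a true size of about 0.034 to 0.037 against 0.041 and gives up about 1 to 2 points of power, or about 3 to 4 men per arm. This compares the planned exact test with an asymptotic stratified one; the least favourable planned-rate case, 15 points off each diagnosis at 120 per arm, reaches 2.6 points. The loss is negligible when the rates are similar and about 4 to 6 points (rates halved) between 10%/50% and 4.5%/59%.

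Type I error is not inflated, and the sample-size calculation and the named test agree with each other. The figures assume exact 50:50 diagnosis balance in each arm and no site effect. Site is also a stratification factor left out of the test, but the article gives nothing from which to quantify its effect.

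**What to change.** Before any unblinded look at the primary endpoint, state that the primary test is an asymptotic Cochran-Mantel-Haenszel test without continuity correction, stratified by diagnosis, at the same 0.0125 and 0.041 levels. Report a Mantel-Haenszel risk difference with its confidence interval. Keep the pooled 2×2 unconditional test as a sensitivity analysis. Do not use an exact conditional stratified test, for the reason in step 7 of the working, and do not add the nine sites as strata if cells would be sparse.

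The cost is a sentence or two in the analysis section, with no extra men or data. There are two downsides. Size control becomes asymptotic instead of exact: simulated size is about 0.041 at the final analysis, but size at the interim look, with only 40 per group, was not simulated and should be confirmed. And between 0 and about 0.4 points of power are lost if the two diagnoses turn out to have equal rates.

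### The sample-size section gives 80% power to both 246 and 240 men and makes its only dropout allowance before randomisation; at 240 men and α = 0.041, power is about 77–78%

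*Protocol article*

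**What the plan says.** All figures are in the Statistical Analysis section of the protocol article.

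- **Two-stage α.** "The α level for the interim look will be .0125, leaving α = .041 for the final analysis".
- **Test.** "The analysis will be done overall using a single 2×2 unconditional test".
- **Requirement (second paragraph).** "For an unconditional test at the two-sided 0.041 significance level, this requires 123 per group, for a total of 246". The design alternative is 30% vs 15% within one year, with 80% power.
- **Target and accrual (third paragraph).** The aim is 240 evaluable men, and "we will accrue a total of 272 subjects, which allows for an estimated dropout rate of 10% during the run-in phase prior to randomization".
- **Power claimed for that plan.** "This will provide us with 80% power for rates of 30% vs. 15" per cent. The same paragraph gives 98% for 30% vs 10%, 87% for 25% vs 10%, 85% for 20% vs 7% and 85% for 15% vs 4%.

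Under Screening, Registration and Run-in Procedures, the run-in lasts 7 to 10 days. The primary endpoint is resolved one year after that. No loss between randomisation and the endpoint is mentioned in the accrual arithmetic.

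**The concern.** Two neighbouring paragraphs give different numbers of men the same power for the same rates, so at least one figure needs correcting. The accrual total does not settle which, because the expected number randomised lies between the two. The only dropout allowance is used up in the first days, before anyone is randomised, while the endpoint needs a further year of participation and a final biopsy.

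The stated power will be relied on. Under Future Directions, the article says that the trial is meant to inform a larger phase III trial. A null result read as coming from an 80%-powered comparison would carry slightly more weight than the design gives it, and more again if an appreciable number of men have no endpoint.

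**Working it through.** **Inputs.** Rates 0.30 and 0.15; final two-sided α = 0.041; interim α = 0.0125 at 40 per group; equal groups; 246 required; 240 evaluable; 272 accrued; 10% run-in loss. All are from Statistical Analysis. The loss after randomisation is not given and is assumed below.

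**1. Reproducing the requirement of 123 per group.** With z(0.041/2) = 2.0435 and z(0.80) = 0.8416, the unpooled normal formula gives

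n = (0.30×0.70 + 0.15×0.85) × (2.0435 + 0.8416)² / 0.15² = 0.3375 × 8.324 / 0.0225 = 124.9.

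The pooled-variance formula gives 128. Power at 123 per group is 79.4% (unpooled normal), 78.4% (pooled normal) and 78.5% (exact unconditional pooled-Z test, with size maximised over the nuisance rate). Counting interim rejections, the exact figure is about 79.0%. So 123 is reproduced within the tolerance of the method.

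**2. Accrual.** 272 × 0.90 = 244.8, about 245 randomised. Against 246 this is about 1 short; 246 / 0.90 = 273.3, so 274 would be needed. Against 240 the margin is 4.8 men, and 4.8 / 244.8 = 2.0%.

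**3. Power at the stated target, 120 per group, α = 0.041.** Pooled normal formula:

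Φ{[0.15√120 − 2.0435√(2×0.225×0.775)] / √0.3375} = Φ{(1.6432 − 1.2068) / 0.5809} = Φ(0.751) = 77.4%.

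The exact unconditional pooled-Z test gives 77.2%, or about 77.8% counting interim rejections. The step from 123 to 120 per group therefore costs about 1 point.

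**4. All five powers in the third paragraph** (exact unconditional pooled-Z, 120 per group):

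| Rates | Stated | α = 0.05 | α = 0.041 |
|---|---|---|---|
| 30% vs 15% | 80% | 79.8% | 77.2% |
| 30% vs 10% | 98% | 97.8% | 97.4% |
| 25% vs 10% | 87% | 87.3% | 85.5% |
| 20% vs 7% | 85% | 85.3% | 83.0% |
| 15% vs 4% | 85% | 85.5% | 82.4% |

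At 0.05 every stated value is matched within 0.5 point. At 0.041 every stated value is too high, by 0.6 to 2.8 points.

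**5. Assumed loss of the endpoint after randomisation**, from 245 randomised, 30% vs 15%, α = 0.041:

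| Assumed loss | Men with endpoint | Per group | Exact | Pooled normal |
|---|---|---|---|---|
| 5% | 245×0.95 = 232.8 | 116 | 74.5% | 75.9% |
| 10% | 245×0.90 = 220.5 | 110 | 73.5% | 73.6% |
| 15% | 245×0.85 = 208.3 | 104 | 70.4% | 71.1% |
| 20% | 245×0.80 = 196.0 | 98 | 68.2% | 68.4% |

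The exact figure at 116 is pulled down by discreteness: the critical value jumps to 2.101 there, against 2.068 at 110. At 115 per group the exact power is 75.8%. A fair reading for 5% loss is 75–76%.

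**The case against.** The strongest reply is that the demonstrable discrepancy is small. The 246/240 mismatch is worth about 1 point of power, and being one or two men short of 246 at randomisation about 0.3 to 0.4 points. The article does not name the statistic behind its unconditional test, so gaps of a point or so may be method or rounding. This stands, and it limits the size of the point. It does not remove the contradiction, and rounding does not easily explain why all five stated powers exceed the 0.041 values and all match 0.05.

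Four stronger readings are tempting and are not supported:

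- **That the plan allows no loss after randomisation.** It leaves 4 to 5 men, about 2%, between the expected number randomised and the 240 target. The margin is thin and unlabelled, but it is not zero.
- **That 123 per group is itself wrong because an exact test gives 78.5%.** Reasonable methods give 78.4% to 79.4%, so the stated requirement is reproduced closely enough.
- **That true power is in the low-to-mid 70s.** That follows only if roughly 5% to 15% of the randomised men have no endpoint, and the article gives no such rate.
- **That the discontinuation rules under Treatment Interruption or Termination imply lost endpoints.** Those rules stop study drug. Table 1 schedules the final biopsy at month 12 or at early termination, so a man who stops drug may still contribute an outcome.

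It is also only an inference that the powers were carried over from a 0.05 calculation; the article does not say so.

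**Conclusion.** The point holds as an inconsistency with a modest, correctable effect. The section requires 246 men, targets 240 and claims 80% for both. For 30% vs 15% at 0.041, 240 evaluable men give about 77–78%. Across the five scenarios the stated powers are 0.6 to 2.8 points too high under an exact unconditional pooled-Z test. The accrual figure covers run-in loss and leaves about 2% for the following year.

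The further fall, to roughly 75–76% at 5% loss, 73–74% at 10%, 70–71% at 15% and 68% at 20%, is conditional. It assumes equal loss in the two groups, unchanged event rates among the men who remain, and a loss rate that the article does not give. It shows how sensitive the plan is and is not an estimate of the trial's power.

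**What to change.** In Statistical Analysis:

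1. Use one evaluable target, 240 or 246, in both paragraphs. Keeping 240 fits the accrual of 272. If 246 is kept, say that 272 is expected to yield about 245.
2. Restate all five powers at α = 0.041 for that number, naming the test statistic and saying whether interim rejections are counted. At 240 the exact pooled-Z values are 77.2, 97.4, 85.5, 83.0 and 82.4%, the first being about 77.8% with interim rejections counted.
3. Say that the 10% covers run-in loss only (272 to about 245 randomised).
4. Add power under a labelled, assumed loss of the primary endpoint after randomisation, for example 5% to 20%, kept separate from stopping study drug.

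This changes wording only. No extra patients and no change in conduct are needed; the cost is a stated power a few points less favourable.
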